#### 2.5.2 Experimental group: heat-sensitive moxibustion plus conventional treatment

(1) Acupoint Selection: Qihai, Guanyuan, Ciliao (bilateral), Yongquan (bilateral).

(2) Acupoint Location: Refer to the national standard of the People’s Republic of China, “Names and Locations of Acupoints” (GB/T123456-2006).

(3) Usage: After urination, the patient should adopt a comfortable posture, exposing the skin at the designated acupoints while ensuring sufficient warmth. The practitioner will then embark on a suspended moxibustion exploration, utilizing a blend of tracing, rotating, pecking, and gentle moxibustion techniques within specific regions: the abdomen (centered on the Ren Meridian, spanning from Qihai to Guanyuan, with a 3 cm radius), the lower back (focusing on both Ciliao acupoints, also with a 3 cm radius), and the soles of the feet (centering on both Yongquan acupoints, maintaining a 3 cm radius). Subsequently, a tracing moxibustion will be administered, where a lit pure moxa stick is held approximately 3 cm away from the patient’s skin and smoothly traversed along the Ren Meridian, Bladder Meridian, and Kidney Meridian. This process continues until the patient experiences a warm sensation along the treatment path, facilitating the clearing and activation of the meridians. This tracing moxibustion phase lasts for 2–3 min. Following this, a rotating moxibustion will be applied to the acupoints for 1–3 min, aiming to warm and stimulate local qi and blood circulation while identifying sensitive points. These sensitive points manifest as various heat-sensitive sensations, including heat penetration, heat expansion, or heat conduction along meridians, among others. Any acupoint that elicits one or more of the nine types of heat-sensitive moxibustion sensations (e.g., warmth in extremities, body warmth, preference for heat, skin erythema, facial flushing or sweating on the forehead, gastrointestinal motility reactions, heat penetration, heat expansion, or non-thermal sensations) is deemed a heat-sensitive acupoint, regardless of its alignment with traditional acupoint locations. The selection of optimal heat-sensitive acupoints follows a specific hierarchy: acupoints with non-thermal sensations are prioritized; those where the heat-sensitive sensations direct or reach the affected area are preferred; and acupoints exhibiting stronger heat-sensitive sensations are given higher priority. Next, a pecking moxibustion will be applied for 1–2 min to intensify the heat sensitivity of the chosen acupoints. This is followed by a gentle moxibustion technique to initiate and propagate the heat-sensitive sensations until they dissipate or significantly diminish.

One treatment cycle consists of 5 days of treatment followed by 2 days of rest, with 2 consecutive treatment cycles being administered. To isolate the effects of the experimental intervention, all enrolled participants (both intervention and control groups) will be instructed to refrain from receiving any additional moxibustion treatments or traditional Chinese medicine therapies (e.g., acupuncture, cupping, herbal medicine) during the 8-week study period. These restrictions were communicated verbally and in written form at enrollment. And participants will be requested to complete weekly diaries to report any inadvertent use of prohibited therapies.

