**FIGURE 1 F1:**
[figure not shown]
The flow chart of the clinical procedures.

**TABLE 1 T1:** Schedule of enrollment, intervention and assessment.

Time point	Enrollment Week -1	Allocation Week 0	Treatment phase Week 1-2	Follow-up Week 3	Follow-up Week 10

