**Primary outcome**					
The frequency of nocturia	–	X	–	X	X

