### 2.7 Procedure

Prior to the commencement of therapy, the practitioner ought to document the patient’s nocturia frequency, administer and record the Pittsburgh Sleep Quality Index (PSQI) and Nocturia Quality of Life (N-QOL) scale scores, assess the traditional Chinese medicine syndrome score, and evaluate the intensity of nocturia and urinary frequency. Upon the morning subsequent to enrollment, fasting blood samples will be procured for the assessment of AVP and ANP levels. Throughout the treatment period, nocturia frequency will be meticulously recorded on a daily basis.

Upon completion of the treatment regimen, the PSQI, N-QOL scale scores, and traditional Chinese medicine syndrome score will be reassessed, and fasting blood samples will be collected the subsequent morning for a repeat analysis of AVP and ANP. Additionally, 2 months post-treatment, these assessments–including the PSQI, N-QOL scale scores, traditional Chinese medicine syndrome score, and fasting blood tests for AVP and ANP–will be conducted once more.

Ultimately, a comprehensive evaluation will encompass the nocturia frequency, sleep quality, quality of life, traditional Chinese medicine syndrome scores, as well as AVP and ANP levels, for both patient cohorts, both pre- and post-treatment, with a further assessment conducted 2 months after the conclusion of therapy. Figure 1 illustrates the clinical procedures during the research.

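### The 8-week ban on other moxibustion and TCM therapies is shorter than the trial: first treatment to the Week-10 visit takes about 9 to 11 weeks

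*Protocol article*

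**What the plan says.** Section 2.5.2 instructs both arms, in order to isolate the effect of the intervention, to "refrain from receiving any additional moxibustion treatments or traditional Chinese medicine therapies (e.g., acupuncture, cupping, herbal medicine) during the 8-week study period". It gives no start date, and no other section defines an 8-week period. On how the rule is conveyed and policed, the same section says "These restrictions were communicated verbally and in written form at enrollment" and that "participants will be requested to complete weekly diaries to report any inadvertent use of prohibited therapies". Section 2.12 keeps users of prohibited therapies in the ITT analysis, flags them for sensitivity analysis, and also analyses the data without protocol violators.

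The calendar comes from three places:

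- Section 2.5.2: "One treatment cycle consists of 5 days of treatment followed by 2 days of rest, with 2 consecutive treatment cycles being administered".
- Table 1: columns headed "Treatment phase Week 1-2" and "Follow-up Week 10", with a further follow-up at Week 3. The primary outcome row, "The frequency of nocturia", and all the listed secondary outcomes are marked at Week 0, Week 3 and Week 10.
- Section 2.7: "with a further assessment conducted 2 months after the conclusion of therapy". Section 2.12 gives the same timing.

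**The concern.** The ban is an operative rule, and its stated length conflicts with the schedule it is meant to protect. If it runs from the start of treatment, participants are free to use acupuncture, herbal medicine or more moxibustion in the last weeks before the final visit. Only that visit can test the durability of effect that section 3 emphasises.

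Use in that gap could move the Week-10 contrast either way. Uptake in the control arm would shrink the difference, and continued moxibustion in the HSM arm would enlarge it. The setting makes such use plausible: the site is a TCM hospital (2.2), eligibility requires a TCM syndrome diagnosis (2.4.1), controls receive lifestyle and exercise advice only (2.5.1), and participants know their allocation (2.11).

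The analysis safeguard is exposed too. The flag in 2.12 depends on what counts as prohibited, and use after the eighth week would not count on a literal reading.

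**Working it through.** **Inputs.** Day 1 is the first treatment day.

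- Length of ban (2.5.2): 8 × 7 = 56 days.
- Treatment (2.5.2): the last session is on day 5 + 2 + 5 = 12, and cycle 2 ends on day 2 × (5 + 2) = 14.
- Last visit (Table 1): Week 10 runs from day 9 × 7 + 1 = 64 to day 10 × 7 = 70.
- Last visit (2.7, 2.12): 2 months after treatment. The article does not convert this to days, so I take 56 days (8 weeks) to 62 days (the longest two calendar months).

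**Can the 8 weeks be reproduced?** Not as the span from first treatment to last visit. The nearest match is follow-up alone: Weeks 3 to 10 inclusive are 10 − 3 + 1 = 8 weeks.

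**Gap if the ban starts on day 1.** With the visit on day V, the uncovered days are V − 56.

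| Visit day V | Basis | V / 7 (weeks) | Gap (days) | Gap / V |
|---|---|---|---|---|
| 64 | first day of Week 10 | 9.1 | 8 | 12.5% |
| 68 | 12 + 56 | 9.7 | 12 | 17.6% |
| 70 | 14 + 56 (also the last day of Week 10) | 10.0 | 14 | 20.0% |
| 76 | 14 + 62 | 10.9 | 20 | 26.3% |

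V exceeds 56 in every row, so no 56-day window covers day 1 to V. V − 56 is also the smallest possible gap for each V, because a 56-day window covers at most 56 of the V days.

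**Other start points.**

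- From enrolment: the ban ends earlier, so the gap before the last visit is longer. I do not quantify this because Table 1 gives only week labels.
- From the end of treatment: the 12 to 14 treatment days are uncovered instead. Follow-up is fully covered only if 2 months means 56 days.

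**Overlap with the outcome windows at the last visit** (ban from day 1; each window assumed to end on day V).

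| Outcome window | V = 64 | V = 68 | V = 70 | V = 76 |
|---|---|---|---|---|
| 72-hour urination diary (2.8.1), 3 days | 3 | 3 | 3 | 3 |
| N-QOL recall (2.8.2), 14 days | 8 | 12 | 14 | 14 |
| PSQI recall (2.8.2), about 30 days | 8 | 12 | 14 | 20 |

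Entries are days after day 56. For example, at V = 64 the N-QOL window is days 51 to 64, of which days 57 to 64 (8 days) fall after the ban. The whole primary-outcome diary lies in the gap in all four cases.

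**The case against.** The mismatch itself is hard to dispute. The objection is to its weight.

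- **It is probably a slip.** The rule applies to all enrolled participants over the study period and exists to isolate the treatment effect. Nothing suggests that the sponsor meant to release patients shortly before the last visit. This is a fair reading, and on it the outcomes are unharmed and only the text is wrong.
- **The 8 weeks may be the follow-up length, mislabelled.** The run-up to the last visit is then covered if 2 months means 8 weeks. The treatment weeks would be uncovered largely in form, since the ban was announced at enrolment and exclusion criterion 9 (2.4.2) removes people already being treated for nocturia. This is possible, but the text calls the 8 weeks the study period, and an entry criterion does not restrict what happens after entry.
- **Diaries and a flag already exist.** They do, and neither carries a time limit of its own, so under-recording is not established. They help less if prohibited use is taken to mean use within the 8 weeks.
- **Day 76 is not in Week 10.** Correct: on Table 1 alone the gap is 8 to 14 days. The 20-day figure comes from the 2-month wording in 2.7 and 2.12 and should be read as the outer limit.
- **The instruction actually given is not shown.** Also correct. The article does not say whether participants were told 8 weeks.

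These points limit the likely harm. None of them makes an 8-week window fit the schedule.

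**Conclusion.** The concern holds. The stated duration is wrong as written, because it cannot cover both treatment and the last assessment from any start point. On a literal reading from first treatment, 8 to 14 days before the last visit are unprotected by Table 1, and 12 to 20 days by the 2-month wording.

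The inconsistency is certain; contamination is not. Harm requires that the 8 weeks are applied literally and that participants then use other therapies. The documents give no uptake rate, so neither the size nor the direction of any bias can be stated. On the start-of-treatment reading the Week-3 contrast is untouched, and what is at risk is the Week-10 contrast. The overlap counts also assume that the 72-hour diary and the recall periods end on the visit day.

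This should be corrected, because the figure sets the length of a rule meant to protect the comparison and the correction is very cheap.

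**What to change.** 1. In 2.5.2, replace the 8-week wording with a restriction that runs from enrolment through the Week-10 visit.
2. Continue the weekly prohibited-therapy diary in both arms to that visit.
3. In 2.12, define the flag as any such use from randomisation to the Week-10 visit.
4. Check the participant material. If it says 8 weeks, re-instruct participants, or ask about use at the Week-10 visit and record the answer for the flag.

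The cost is wording, one question at the Week-10 visit and, if diaries now stop at week 8, about one to three more diary pages per patient. Sample size, visits and analysis methods do not change.

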### 2.6 Treatment of adverse reactions

If blisters or burns arise locally due to excessive moxibustion or accidental mishandling, promptly administer a specialized burn ointment. For minor blisters, no specific treatment is necessary. However, for larger blisters, fluid extraction is imperative. Following fluid extraction, ensure the affected areas are covered with sterile gauze to protect them from water and prevent infection. In cases of severe conditions, seek medical attention promptly.

### 2.7 Procedure

Prior to the commencement of therapy, the practitioner ought to document the patient’s nocturia frequency, administer and record the Pittsburgh Sleep Quality Index (PSQI) and Nocturia Quality of Life (N-QOL) scale scores, assess the traditional Chinese medicine syndrome score, and evaluate the intensity of nocturia and urinary frequency. Upon the morning subsequent to enrollment, fasting blood samples will be procured for the assessment of AVP and ANP levels. Throughout the treatment period, nocturia frequency will be meticulously recorded on a daily basis.

Upon completion of the treatment regimen, the PSQI, N-QOL scale scores, and traditional Chinese medicine syndrome score will be reassessed, and fasting blood samples will be collected the subsequent morning for a repeat analysis of AVP and ANP. Additionally, 2 months post-treatment, these assessments–including the PSQI, N-QOL scale scores, traditional Chinese medicine syndrome score, and fasting blood tests for AVP and ANP–will be conducted once more.

Ultimately, a comprehensive evaluation will encompass the nocturia frequency, sleep quality, quality of life, traditional Chinese medicine syndrome scores, as well as AVP and ANP levels, for both patient cohorts, both pre- and post-treatment, with a further assessment conducted 2 months after the conclusion of therapy. Figure 1 illustrates the clinical procedures during the research.

### 2.8 Outcome measures

#### 2.8.1 Primary outcomes

The frequency of nocturia: 72-hour urination diary.

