**Method:**

This study is designed as a randomized, single-blind clinical trial, focusing on a population of 110 patients aged 60 and above who suffer from non-specific nocturia lasting for at least 1 month. Patients in the intervention arm are scheduled for 2 cycles of HSM, while patients in the control group will undergo the same cycle of conventional treatment. To ensure objectivity, assessors and investigators will remain blinded to the randomization process. The primary outcome of this study is the reduction in the frequency of nocturia. Additionally, several secondary outcomes will be evaluated, including sleep quality, quality of life scores, the efficacy of traditional Chinese medicine (TCM) syndrome, and changes in blood biomarkers Arginine vasopressin (AVP) and Atrial natriuretic peptide (ANP). These assessments will be conducted at baseline, post-intervention and at the 2-month follow-up to comprehensively evaluate the effectiveness and safety of HSM.

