### 2.3 Research hypothesis

Primary hypothesis: HSM groups will experience significant improvement in the frequency of nocturia.

Secondary hypothesis: HSM groups are anticipated to exhibit notable enhancements in sleep quality, quality of life, as well as traditional Chinese medicine (TCM) syndrome scores.

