### 2.12 Data collection and analysis

The data of various observation indicators of patients were collected on the day of treatment, the day after the end of treatment and 2 months after the end of treatment. To ensure the accuracy and completeness of the data, we will adopt a double-entry method. PASW Statistics 18.0 software was used to establish a database for case investigation data that met the inclusion criteria, and data review was performed after data entry was completed.

The statistical analysis of the PASW Statistics 18.0 data was performed, encompassing descriptive statistics for clinical baseline data. For continuous outcomes, group differences will be analyzed using Student’s *t*-tests if data are normally distributed; otherwise, the Mann-Whitney U test will be applied. For categorical variables, Chi-square tests or Fisher’s exact tests will be used as appropriate. Efficacy evaluations utilized both intention-to-treat (ITT) and per-protocol (PP) populations, while safety assessments were conducted on the safety analysis set. In the intention-to-treat analysis, missing data due to withdrawal or dropout will be handled using the last observation carried forward (LOCF) method. Participants who received prohibited therapies were retained in the trial per the ITT principle but flagged for sensitivity analysis. Their data were analyzed both within the full cohort and in a subgroup excluding protocol violators. When necessary, multiple imputation methods will be considered for missing value replacement, or alternative approaches will be selected based on actual circumstances. For clustering, the K-MEANS clustering method was utilized, while applying Pearson or Spearman correlation analysis to examine correlations. A *P*-value of 0.05 or less was considered statistically significant.

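### The primary outcome is measured at two post-baseline visits of equal standing and tested at 0.05, with no primary visit, order of testing or deciding analysis set named.

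*Protocol article*

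**What the plan says.** - **Outcome.** Section 2.8.1 consists of the variable and the instrument: "The frequency of nocturia: 72-hour urination diary". The abstract adds direction but no visit: "The primary outcome of this study is the reduction in the frequency of nocturia".
- **Visits.** Table 1 marks the primary outcome at Week 0, Week 3 and Week 10, and has a dash for the treatment phase. Section 2.7 describes the pre- and post-treatment evaluation "with a further assessment conducted 2 months after the conclusion of therapy", without ranking the two later readings.
- **Analysis sets and threshold.** Section 2.12 states: "Efficacy evaluations utilized both intention-to-treat (ITT) and per-protocol (PP) populations". It plans tests of group differences (Student's t or Mann-Whitney U) and one rule for significance, a P-"value of 0.05 or less was considered statistically significant". It gives no order of testing.
- **Hypothesis.** Section 2.3 reads: "HSM groups will experience significant improvement in the frequency of nocturia". It names no comparator.

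**The concern.** The time point is part of what defines a primary outcome. Here two readings of the same variable could each be presented as the primary result once the data are seen. The Discussion does not settle the matter: it stresses maintenance of effect at 2 months, which could justify leading with Week 10, while the schedule equally allows leading with Week 3. The unranked ITT and PP sets leave a second, smaller choice of the same kind.

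At stake is the error rate behind a claim of efficacy. A reader of the final report could not tell whether a result at one visit was the planned test or the better of two.

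**Working it through.** **1. The plan's own figure.** The only related figure is the sample size in section 2.9. With Z = 1.96, P = 0.5 and E = 0.10:

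Z² × P × (1 − P) / E² = 3.8416 × 0.25 / 0.01 = 96.04, stated as 96.

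96 × 1.15 = 110.4, stated as 110.

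This is the precision formula for a single proportion. The quoted power of 0.90 does not enter it, and it involves no visit and no between-arm contrast. The sample size section therefore cannot be used to infer which visit is primary.

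**2. Two visits, one analysis set.** The inputs are two tests at 0.05 two-sided (Table 1, sections 2.9 and 2.12). The correlation ρ between the two test statistics is not in the document and is assumed. When HSM adds nothing:

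P(at least one significant) = 2 × 0.05 − P(both significant).

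Counting only results that favour HSM, 0.025 replaces 0.05. P(both) comes from the bivariate normal distribution.

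| ρ (assumed) | Two-sided: 0.10 − P(both) | Favouring HSM: 0.05 − P(both) |
|---|---|---|
| 0 | 0.10 − 0.0025 = 9.75% | 0.05 − 0.0006 = 4.9% |
| 0.5 | 0.10 − 0.0093 = 9.1% | 0.05 − 0.0046 = 4.5% |
| 0.7 | 0.10 − 0.0165 = 8.35% | 0.05 − 0.0083 = 4.2% |
| 0.8 | 0.10 − 0.0219 = 7.8% | 0.05 − 0.0110 = 3.9% |

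The nominal rates are 5% and 2.5%.

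**3. Two visits by two sets.** If PP keeps 85% of participants (the complement of the 15% dropout in section 2.9), the ITT and PP statistics correlate at about √0.85 = 0.92. A range of 0.92 to 0.95 is assumed. Simulation with 1,000,000 draws gives:

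| ρ between visits (assumed) | Two-sided | Favouring HSM |
|---|---|---|
| 0 | 12.5–13.2% | 6.4–6.7% |
| 0.5 | 11.6–12.3% | 5.8–6.1% |
| 0.9 | 9.0–9.5% | 4.5–4.7% |

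The 18.5% that four independent tests would give is not realistic, because PP is nested within ITT. In the scenarios shown, the second set adds less than the second visit does when ρ is low.

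**4. Which three nights.** Section 2.12 collects data on the day after treatment ends, while Table 1 places the reading in Week 3. Section 2.5.2 gives two cycles of 5 treatment days and 2 rest days. If sessions start on day 1 of Week 1, the last session is on day 5 + 2 + 5 = 12.

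- If treatment ends with the last session, the day after is day 13, still in Week 2. A diary handed in then covers mostly treatment nights.
- If treatment ends with the cycle on day 14, the day after is day 15, in Week 3. A diary handed in then covers roughly the nights after days 12 to 14.

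Both readings are possible, so the window is unsettled. The two statements do not contradict each other.

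**5. Cost of the alternatives.** Splitting alpha so that each visit is tested at 0.025 would cut a 90% power to about 84% per visit. At 55 per group, the standardised difference detectable with 90% power would rise from 0.62 to 0.67. Testing in a fixed order keeps the full 5% for the first test.

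**The case against.** **This belongs in the analysis plan.** Handling of multiplicity and ranking of analysis sets often do. The primary time point does not: it belongs to the definition of the outcome, and the article gives that definition a section of its own.

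**ITT is evidently the main set.** Running ITT and PP side by side is routine. Section 2.12 keeps users of prohibited therapies in the trial on the ITT principle and treats their exclusion as a sensitivity analysis, which leans towards ITT. This largely stands. What is missing is a sentence saying that ITT decides.

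**No sentence says that success at either visit is enough.** True. The error rates above are conditional on that use of the results. The document does not license it, but does not rule it out.

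**The favourable-direction rate for two visits stays below 5%.** Also true. It should be compared with the nominal 2.5%.

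Three stronger readings are tempting and are not supported:

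- A reader might infer from section 2.3 that a pre-post gain in the HSM arm alone would count as success. Section 2.12 plans tests of group differences and describes no within-arm test, so this is a mismatch of wording.
- A reader might take "Throughout the treatment period, nocturia frequency will be meticulously recorded on a daily basis" (section 2.7) as a third version of the endpoint. Section 2.8.1 fixes the 72-hour diary, and Table 1 has no primary reading during treatment.
- A reader might say that a 72-hour diary cannot fit collection on the day after treatment. A diary handed in that day can cover the preceding 72 hours.

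**Conclusion.** The point holds as one about an unranked primary outcome. The document gives two equal post-baseline readings, one unadjusted threshold and no formally named deciding set. If either visit can carry the claim, the two-sided error is about 7.8% to 9.75%, or about 3.9% to 4.9% against 2.5% in favour of HSM. This rests on assumed correlations of 0.8 to 0. Letting PP decide as well adds to it, by an amount that depends on a further assumed correlation.

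The inflation is moderate and does not invalidate the design. It should be corrected because correction is cheap now, and because once results are known the choice of visit cannot be shown to be independent of them.

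**What to change.** 1. Name one primary test: the between-arm difference in mean nightly voids from the 72-hour diary at one visit, adjusted for the Week 0 value already collected, in all randomised participants (ITT), at two-sided 5%. Use Week 3, or Week 10 if durability is the main claim.
2. Test the other visit second, only if the first is significant. Make PP supportive.
3. State which three nights the post-treatment diary covers, and reconcile the collection day in section 2.12 with Week 3 in Table 1.
4. As a wording correction, phrase section 2.3 as a greater reduction with HSM plus conventional treatment than with conventional treatment alone.

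**Cost.** No extra visits or participants are needed. A positive result at the second visit after a negative first is no longer confirmatory. The baseline-adjusted model replaces the planned unadjusted t-test or Mann-Whitney test for the primary outcome, so this is more than a change of wording. Section 2.2 schedules the trial from January 2024 to December 2025, so diaries may already have been completed. The stated window should describe the nights actually recorded. Make the change before unblinded data are examined.
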